### Ethical and Health Research Authority approval

This study was reviewed and received a favourable ethical opinion by Wales Research Ethics Committee (REC) 2 on 13 September 2016 (Reference: 16/WA/0248) and host site approval was received from East London Foundation NHS Trust R&D office, via Noclor on 27.09.2016. All information collected will be kept confidential, stored securely and archived in accordance with the research governance policy of the sponsor. Participant anonymity will be retained by allocating a unique identification number for the trial and any identifiable information stored separately from this.

### Trial governance, monitoring and auditing

The Trial Management Group (TMG) consists of the chief investigator, study team and co-investigators and will provide overall management of the study including set-up, training, recruitment, promotion of the study and interpretation of results. Given the small and exploratory nature of the trial, no interim analysis is planned. Further to consultation with the study sponsor, the team considers that the nature of the intervention does not pose a significant risk to the study participants, and therefore we will not use a data monitoring committee. An Independent Advisory Panel (IAP) consisting of two independent members will monitor the conduct of the trial and meet four times over the course of the study to discuss research progress according to defined milestones, emerging difficulties and dissemination of results.

The chief investigator in liaison with the sponsor and the IAP has ultimate authority to halt the study or withdraw individual participants should concerns arise during the study. Adverse events will be monitored and recorded throughout. All serious adverse events will be reported to the sponsor and reported to the REC if assessed to be serious, related to the study and unexpected. Adherence to the protocol and any subsequent amendments will be supervised by the sponsor. Access to data will be granted to authorised representatives from the sponsor, host institution and the regulatory authorities, to permit trial-related monitoring, audits and inspections.

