### Design considerations

For comparison we have chosen to use a wait-list control. This will enable us to compare the intervention to treatment as usual, with the option for those in the control group to receive group music therapy at the study end.

We propose offering three sessions per week to participants for a number of reasons. First, in a previous study in a similar environment [37] there were high rates of attrition in the once-per-week group. Our previous research within an acute inpatient environment demonstrated that offering an increased frequency was acceptable, of therapeutic benefit and increased the chances of attending a greater number of music therapy sessions [53]. Second, given the potential difficulties in motivation and attending sessions, the increased frequency may help to build momentum and keep attendance going. Greater frequency also means it may be possible to develop a greater stability of group membership, which will help to foster trust and commitment in the group and, in the case of ongoing songwriting and performance work, provide opportunities to progress these longer-term activities. In total, 42 sessions are available to participants, which may enable us to detect a large effect on depressive symptoms, and medium-to-large effects on general symptoms [34].

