### Intervention

The intervention has been described in full in a manual developed for the purposes of this study and has been informed by existing manuals for group songwriting [44], individual psychodynamic music therapy for depression [30, 47] and principles of resource-oriented music therapy [48]. The intervention was developed through focus group discussions with music therapists, psychologists and service users with a diagnosis of depression and was finalised in team discussions with music therapists and Heads of Arts Therapies involved in the study. The Template for Intervention Description and Replication [63] and Standard Protocol Items: Recommendations for Interventional Trials (SPIRIT) [64] checklists are attached as Additional files 1 and 2. The intervention manual and full study protocol are available on request from the authors.

Group music therapy will be provided three times per week over 14 weeks by two HCPC-registered music therapists. Each session will last 90 minutes and will comprise warm-up activities moving to sharing of pre-known songs and improvisation. Therapists will move from improvisation into songwriting, which will then be the main focus for the remainder of the session. Opportunities will be offered after each activity for verbal reflection. The last 15 minutes will be dedicated to reviewing the session and may include playing through a final piece of music.

The intervention will be provided in a community centre within the locality of Newham. The community centre is a non-NHS site and offers facilities for additional social contact such as a café and wider non-medical community groups. Music therapists will receive weekly clinical supervision from the chief investigator.

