### Randomisation

Randomisation will occur once all 30 participants have been recruited and baseline measures have been completed. In order to obtain sufficient data on the intervention, we will utilise simple block randomisation with unbalanced allocation so that 20 participants receive the intervention and 10 are allocated to the wait-list control group. A researcher independent of the study team will perform the randomisation using the Experimental Design Generator and Randomiser (EDGAR-II) [65] and inform the music therapists and unblinded member of the study team of the allocation by email. The music therapists will then inform participants of their allocation and provide additional support if required.

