Self-report:4.Self-reported symptoms of depression as measured by the Beck Depression Inventory II (BDI-II) [69–71]5.Psychological distress as measured by the Brief Symptom Inventory (BSI) [72]6.Self-esteem as measured by the Rosenberg Self-Esteem Scale (RSES) [73–75]7.Perceived self-efficacy as measured by the General Perceived Self-Efficacy Scale (GPSES) [76–78]8.Satisfaction with treatment in community services as measured by the Client Satisfaction Questionnaire (CSQ) [79]9.Work and social adjustment as measured by the Work and Social Adjustment Scale (WSAS) [80]10.Quality of life as measured by the Manchester Short Quality of Life Scale (MANSA) [81, 82]11.Receipt of services as measured by the Client Services Receipt Inventory (CSRI) [83, 84]

Our proposed clinical endpoint is the week post-intervention, with secondary endpoints at 3 and 6 months post-intervention. Process measures of attendance, self-reported depression symptoms (BDI-II [69]) at weeks 3, 6 and 9 and weekly mood pre-session and post-session (Dispositional Mood Scale (DMS) [85, 86]) and group relationships (Relationship Satisfaction Scale (RSS) [87]) will be measured.

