**Fig. 2 Fig2:**
[figure not shown]
Standard Protocol Items: Recommendation for Interventional Trials (SPIRIT) diagram of assessments at enrolment, allocation, 3-weekly sessions, post-intervention, 3-month and 6-month time points. ^a^Administered in the intervention group only. ^b^Rated pre-session and post-session. *BDI-II* Beck Depression Inventory-II, *CSQ* Client Satisfaction Questionnaire, *CSRI* Client Services Receipt Inventory, *DMS* Dimensional Mood Scale, *GPSES* General Perceived Self-efficacy Scale, *IIM* Interest in Music Scale [95], *LSP* Life Skills Profile, *MADRS* Montgomery-Åsberg Depression Rating Scale, *MANSA* Manchester Short Quality of Life Scale, *RSES* Rosenberg Self-esteem Scale, *RSS* Relationship Satisfaction Scale, *WSAS* Work and Social Adjustment Scale

Baseline assessments will occur as soon as possible after informed consent is obtained. Follow-up visits will be arranged in the week following the end of the intervention, and at 3 and 6 months after the intervention end. Participants in the intervention arm will each receive a payment of £10 to contribute towards travel costs and participants in the wait-list control group will each receive £15 in the form of shopping vouchers. Participants will be eligible to receive assistance with the cost of transport to and from therapy sessions if they currently do not receive such help.

Researchers conducting blind follow-up assessments will enter the data onto paper case report forms designed for each assessment. These will be transferred into an electronic database and double-entered. Limits are set on data values to be entered to ensure only valid entries are permitted.

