#### Clinical outcomes

This study will employ intention-to-treat analysis. Data from all subjects will be included in the analysis as randomised. Adverse events will be reported by sub-groups of those who were currently receiving the intervention and those who were not.

We will first calculate a mean value of the outcome for each unit and present them with confidence intervals. Outcomes will be compared between intervention and control groups using linear regression models, adjusting for the baseline score of the given outcome. The confidence limits of each treatment effect and knowledge of the clinically important difference (where this is available) will be used to determine whether clinically important differences are ruled out by these confidence limits. The intra-cluster correlation coefficient will be calculated. Due to the small sample size, this estimate is likely to be imprecise, therefore we will also use estimates in the literature from similar studies for comparison to inform the design of any future studies. We will descriptively explore in sub-group analyses whether there are any differences between compliant and non-compliant attenders, responders and non-responders and whether any socio-demographic and clinical characteristics are associated with outcomes. As a preliminary economic evaluation, we will calculate the cost of delivery of music therapy and cost of services received by both groups using the CSRI [83]. This will be descriptive only to provide an estimate for future studies.

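### Adverse events are reported by time on and off therapy, a split that nearly matches how closely participants are observed, so an apparent excess on therapy could be detection alone

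*Protocol article*

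**What the plan says.** Two sentences govern adverse events. Trial governance, monitoring and auditing states: "Adverse events will be monitored and recorded throughout". Clinical outcomes, under Statistical analysis, fixes how they are tabulated: "Adverse events will be reported by sub-groups of those who were currently receiving the intervention and those who were not". The grouping is thus by therapy status at the time of the event, not by randomised arm.

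Contact on therapy is set under Intervention: "Group music therapy will be provided three times per week over 14 weeks by two HCPC-registered music therapists". Design considerations gives the total: "In total, 42 sessions are available to participants". Contact with everyone is set under Data collection: "Follow-up visits will be arranged in the week following the end of the intervention, and at 3 and 6 months after the intervention end". Allocation is such that "20 participants receive the intervention and 10 are allocated to the wait-list control group". Wait-list participants become eligible for therapy only after their 6-month follow-up, so within the follow-up period all on-therapy time comes from the intervention arm.

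One further schedule is open. Outcome measures and endpoints lists "self-reported depression symptoms (BDI-II [69]) at weeks 3, 6 and 9" without naming an arm. A footnote to Fig. 2 reads "Administered in the intervention group only", but the figure is not shown, so the measures it marks cannot be identified.

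**The concern.** The variable chosen to split the adverse-event table nearly coincides with the intensity of observation. A participant in the therapy course is in front of two therapists up to three times a week. Mood and group relationships are rated around sessions, sessions are videoed, and the therapists share in judging mental state and risk when discontinuation is considered. These session-based channels have no counterpart off therapy. They are also unblinded, whereas the follow-up assessors are blind.

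If true event rates were equal, a table built this way could still show more events on therapy, and nothing in it would tell the reader whether that was harm or closer watching. The trial is meant to inform the design of a full trial and has no data monitoring committee, so readers will look at these two columns even though no test is planned. Regrouping the same events by randomised arm would not cure this, because session-observed events would still arise in one arm only.

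**Working it through.** **The plan's own figure.** 3 sessions per week × 14 weeks = 42, as Design considerations states. The protocol gives no adverse-event rate, so there is none to reproduce.

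**Person-time.** Inputs: 20 and 10 participants; a 14-week course; 6 months of follow-up taken as 26 weeks. Assumptions: no early discontinuation, and the post-intervention visit counted as off therapy because it falls in the week after the course.

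- On therapy: 20 × 14 = 280 person-weeks.
- Off therapy, intervention arm after its course: 20 × 26 = 520.
- Off therapy, wait-list arm: 10 × (14 + 26) = 400.
- Total off therapy: 520 + 400 = 920, of which 520 / 920 = 57% is the intervention arm.

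**Scheduled contacts per person-week.**

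- On therapy, all sessions attended: 20 × 42 / 280 = 3.0.
- On therapy at 14 sessions, the attendance benchmark in Table 1: 20 × 14 / 280 = 1.0.
- Off therapy, three visits each: 30 × 3 / 920 = 90 / 920 = 0.098.
- Off therapy if the wait-list arm is also seen at weeks 3, 6 and 9: (90 + 10 × 3) / 920 = 120 / 920 = 0.130.

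| Sessions attended | Ratio, no wait-list contact at weeks 3, 6, 9 | Ratio, with those contacts |
|---|---|---|
| 42 | 3.0 / 0.098 = about 31 | 3.0 / 0.130 = about 23 |
| 14 | 1.0 / 0.098 = about 10 | 1.0 / 0.130 = about 7.7 |

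No reading of the visible schedule brings the two close to equal.

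**By randomised arm.** Over the whole study the intervention arm has at most 42 + 3 = 45 scheduled contacts per person, or 14 + 3 = 17 at the benchmark. The wait-list arm has 3, or 6 if the week 3, 6 and 9 measures reach it. Within the 14 weeks the wait-list count is 0 to 3.

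**From contact to counts.** Observed ratio = true ratio × (capture on therapy / capture off therapy). With a true ratio of 1, the observed ratio is the capture ratio alone. The protocol gives no capture rates, so these are assumptions:

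- 80% against 60%: 0.80 / 0.60 = 1.3.
- 95% against 40%: 0.95 / 0.40 = 2.4.
- 90% against 90%, 60% or 30%: 1.0, 1.5 or 3.0.

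The contact ratios above are not capture ratios. A participant seen ten times as often does not yield ten times the events.

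**The case against.** The strongest objection is that this is a condensed article. Adverse-event forms and intervals normally sit in the full protocol, which the authors offer on request, and a common question set may already be there. That stands as far as the collection procedure goes, and its absence from the article is not the finding. The tabulation rule, however, is published and stands by itself. A common question set elsewhere would help only if session-observed events were kept out of the comparison.

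A reader might infer that wait-list participants are not observed at all during the course, 42 contacts against none. The document does not support that. The week 3, 6 and 9 BDI-II has no stated arm. Service receipt is assessed in both arms during the period (Wait-list control), clinical teams are kept in contact (Ancillary and post-study care), and regular contact with participants is named as a retention measure (Discussion). These routes may reach the wait-list arm. None is described as an adverse-event enquiry, and service use would miss distress that leads to no service contact.

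A reader might also take the off-therapy column to be the wait-list arm. It is not, since more than half of it is the intervention arm after its course. That time is sparsely observed too, so the contrast between dense and sparse observation remains.

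It is fair, too, that the plan reports adverse events descriptively and specifies no test or rate ratio, that Table 1 has no adverse-event criterion, and that the bias would tend to overstate harm. These points limit the consequence. They do not make the two columns comparable.

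**Conclusion.** The concern holds in a limited form. As written, the on/off-therapy table sets about 3.0 scheduled contacts per person-week (1.0 at 14 sessions) against about 0.1, so an apparent excess on therapy could be detection alone. This rests on the stated schedule, full follow-up and a 26-week reading of 6 months. It survives the more favourable reading of the week 3, 6 and 9 measures, where the ratio is still 7.7 to 23.

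The size of any spurious excess cannot be derived from the document. The range of 1.3 to 2.4 is an illustration that depends wholly on assumed capture rates. The protocol makes no formal safety inference, so this is a worthwhile and cheap improvement to a descriptive table. It does not undermine the trial's feasibility aims.

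**What to change.** In Clinical outcomes, state that the between-arm adverse-event summary is by randomised arm and uses only events captured the same way in both arms:

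- one identical structured question set at the existing post-intervention, 3-month and 6-month visits, worded without reference to sessions so that assessors stay blind;
- hospital admissions, which are already a listed outcome.

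List events observed at sessions separately, labelled by source, and do not set them against the control arm.

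The cost is a few lines of analysis text and one common item on the follow-up forms, with no extra visit or staff. The downside is that the comparable set relies on recall over weeks to months, so its counts will be lower. No event is lost, because session-observed events are still listed.

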### Ancillary and post-study care

The music therapists and researchers will maintain contact with the participants’ clinical care teams throughout the study and immediately raise any areas of concern or need. Participants will be offered time to speak with music therapists at the end of the intervention and will be provided with information on music therapy groups and wider music-making opportunities available in the community.

## Discussion

The burden of depression upon society is well-recognised, both in human emotional and economic costs. For those suffering from chronic depression, options for treatment are few for a condition that can last approximately 5 to 20 years [4, 10]. Current evidence on music therapy in mental health suggests it may be an acceptable and tolerable intervention, which may offer a different experience from currently recommended treatment. However, there is no evidence on the effectiveness and cost-effectiveness of such an intervention within an NHS community context.

Building evidence for a complex intervention, such as music therapy, requires more than just an adequate trial design. The intervention requires a clear definition and model, and may require subsequent steps to refine this once examined in practice [57]. Wider research into music therapy has pointed to the importance of training of therapists in the research and intervention procedures [60]. This study will examine not only the practicalities of trial design (in terms of recruitment strategy, retention and outcome measurement) but will also provide a platform upon which the intervention can be specified for the particular needs of patients with long-term depression. Such findings can be immediately integrated and applied in wider music-therapy community mental health work.

Whilst we believe that the intervention may be appealing for those with long-term depression, we anticipate challenges in both maintaining attendance and retaining participants within the study. Measures to address this include assistance with transport costs and maintaining regular contact with participants. Whilst participants may have access to around 42 sessions, this will occur in a relatively short time frame of 14 weeks and it remains to be seen whether changes can be detected within our proposed measures.

### Trial status

The SYNCHRONY study began recruitment on 27 September 2016 with the intervention planned to start mid to late November 2016. The study will be a first step towards refining and testing the effectiveness and cost-effectiveness of group music therapy for long-term depression. Whilst the study is limited in its small scale and single locality, outcomes will contribute to a better understanding of how best to provide music therapy for this patient population and will enable realistic and feasible plans to be made for a future large-scale trial.

## Abbreviations

BDI-II: Beck Depression Inventory-II
BSI: Brief Symptom Inventory
CBASP: Cognitive behavioural analysis system of psychotherapy
CMHT: Community Mental Health Team
CSQ: Client Satisfaction Questionnaire
CSRI: Client Services Receipt Inventory
DMS: Dispositional Mood Scale
EDGAR-II: Experimental Design Generator and Randomisor - II
GP: General Practice
GPSES: General Perceived Self-efficacy Scale
HCPC: Health and Care Professions Council
IAP: Independent Advisory Panel
IAPT: Improving Access to Psychological Therapies
ICD-10: International Classification of Diseases, 10^th^ Edition
IPT: Interpersonal psychodynamic therapy
LSP: Life Skills Profile
MADRS: Montgomery-Åsberg Depression Rating Scale
MANSA: Manchester Quality of Life Scale
NHS: National Health Service
PIC: Participant Identification Centre
REC: Research Ethics Committee
RSES: Rosenberg Self-esteem Scale
RSS: Relationship Satisfaction Scale
SPIRIT: Standard Protocol Items: Recommendation for Interventional Trials
TIDier: Template for Intervention Description and Replication
TMG: Trial Management Group
UK: United Kingdom
WSAS: Work and Social Adjustment Scale
